**11.6.2. Clinical Trial Procedures**

1. **Screening <Visit 1>**

Patients diagnosed with adenomyosis through MR or US imaging are referred to this clinical trial by a gynecologist or interventional radiology department. They will be enrolled in this clinical trial if they satisfy all of the inclusion/exclusion criteria and sign the written consent form voluntarily after being given sufficient explanation on this study.

At the Screening visit, in addition to the inclusion/exclusion criteria, demographic survey, vital signs, physical examination, past medical history, blood tests, pregnancy tests, ECGs, MRIs, ultrasound tests, and questionnaires are used to evaluate the degree of menstrual pain and menorrhagia. The ability to communicate with the investigator and willingness to comply with the clinical trial will also be assessed during the Screening period.

Pre-procedure MRI

An intravenous catheter may be inserted prior to the procedure in order to obtain MRI images before and after using the contrast medium as well as the T1- and T2-weighted images for 3 orthogonal planes, and to administer drugs such as MR contrast agents and weak stabilizers.

Pre-procedure MRI is the final step in determining inclusion/exclusion. For post-treatment MR imaging, a contrast medium commonly used for gynecological imaging in hospitals will be used according to the product manual. (Follow the standard procedure of the hospital)

ALPINION Medical Systems Co., Ltd. 24/45

[figure not shown]

[figure not shown]

Protocol No. APM-03 Version 1.10/Date 20180103

[figure not shown]

1. **Procedure day <Visit 2>**

- HIFU Treatment Protocol

The US-guided HIFU procedure is expected to take 2 to 4 hours, including recovery time (1 to 2 hours) after the procedure is completed. The duration for which the subject remains immobile should be limited to about 3 hours to reduce the risk of deep vein thrombosis (DVT).

- Preparation

1. Based on the selected area, the following HIFU irradiation method can be configured in detail.
   - Focal Point Grid: The spacing (X, Y) between points and the Cartesian (lattice) and Cylinder (cylinder) type focal point placement can be configured.

- - Acoustic Power : Acoustic Power (Intensity)
  - PRF (Pulse Repetition Frequency) : Number of irradiation per second
  - Duty : The duration of the irradiation is configured in units of percentage in the time interval between irradiation.
  - Exposure Time : Duration of irradiation on one focal point
  - Point to Point : Travel time between points
  - Cooling Time : Travel time between slice images
  - Generate Points: A focal point is automatically created in a pattern of Cartesian (lattice) and Cylindrical (cylindrical) in the desired area.
  - Add Point: You can manually create focal points that do not have a uniform pattern in a desired area one by one.

1. Based on the treatment plan of the subject set in the preceding step, simulation is performed before actual treatment to check the validity of the treatment plan.
2. Pre-targeting is performed to test the accuracy of the HIFU irradiation before treating the subject. In pre-targeting, the user arbitrarily sets the location to be irradiated, and actually irradiates the HIFU weakly to check its accuracy through the irradiation location information.

- Treatment Procedure

The operator performs HIFU treatment according to a pre-established treatment plan, and observes the necrosis of the lesion and the progress of treatment through ultrasound images and software. If the position of the uterus is shifted due to urine filling in the bladder, adjust the treatment position and start again. Upon completion of the planned treatment of the entire site, a record of the entire treatment is kept in the subject record.

- After Treatment

When the treatment is completed according to the initially set treatment range, the surgeon acquires an image of the treatment area through ultrasound and MRI to check the planned volume and the range of the treatment volume, and observes for any adverse reactions including changes in the skin. Subjects may be discharged from the hospital on the day of treatment or the next day if there is no abnormality after observing the passage of 1 to 2 hours in the recovery room, and fill out a questionnaire about satisfaction with the procedure before discharge.

1. **Follow-up Period <Visit 3, 4>**

■ Visit 3 (1 month after treatment)

Visit the clinic and perform the following tests

■ Measurement of uterus size (MRI)

- Ultrasound test
- Blood test and FSH test
- Completion of questionnaire: Dysmenorrhea Relief and Dysmenorrhea/Menorrhagia Scores, Quality of Life (SF36-v2, UFS-QoL)

ALPINION Medical Systems Co., Ltd. 26/45

[figure not shown]

[figure not shown]

Protocol No. APM-03 Version 1.10/Date 20180103

[figure not shown]

■ Adverse event/Serious adverse event check

- Concomitant drugs check

■ Visit 4 (3 months after treatment)

Visit the clinic and perform the following tests

■ Measurement of uterus size (MRI)

- Ultrasound test
- Pregnancy test
- Completion of questionnaire: Dysmenorrhea Relief and Dysmenorrhea/Menorrhagia Scores, Quality of Life (SF36-v2, UFS-QoL)
- Adverse event/Serious adverse event check
- Concomitant drugs check

**11.6.3. Concomitant Therapy**

Drugs that may affect the treatment of adenomyosis (see Contraindicated Drugs below) or alternative treatments are prohibited. All drugs already being taken due to underlying diseases are recorded at the time of Screening. Only the drugs added thereafter are recorded in the CRF. If any of the above contraindicated drugs or alternative treatments were received during the clinical trial period, they will be withdrawn from the study and the reason for withdrawal should be recorded.

However, even if it is a contraindicated drug, if a one-time administration is necessary regardless of this study, it can be used within the extent that does not affect the procedure result at the discretion of the investigator and the related information is recorded in the concomitant drugs section of the CRF.

Subjects are administered midazolam and fentanyl for sedation prior to the procedure. The dosage of midazolam and fentanyl is determined by the investigator in consideration of the age and clinical condition of the subject, but generally midazolam 3mg/3ml or 5mg/5ml, and fentanyl 100mcg/2ml are administered. At the discretion of the investigator, analgesics, sedatives and local anesthetics may be administered according to the standard procedure of the institution in consideration of the subject's condition.

**Contraindicated Drugs**

Estrogen (including combined equine estrogen), progesterone, steroids (including corticosteroids), oral contraceptives, etc.

**11.6.4. Study Budget**

Expenses paid by the subject before being referred to this clinical trial are applied retroactively and are not compensated, and expenses incurred after participating in the clinical trial (electrocardiogram, laboratory test, pregnancy test, MRI, U/S, US-HIFU procedure), etc. will be paid by the investigator. In addition, in relation to the time required for participation in this clinical trial, compensation will be made by direct bank transfer in the amount of KRW 100,000 for those residing in the area near the site every visit (Visit 3 and 4), and KRW 200,000 for those residing outside the area of the site. Payment details will be managed through the subject's compensation payment log. Compensation for subjects will not be conditional on their participation in the clinical trial to the end.

ALPINION Medical Systems Co., Ltd. 27/45

[figure not shown]

[figure not shown]

Protocol No. APM-03 Version 1.10/Date 20180103

[figure not shown]

1. **Study Assessment**

**12.1. Efficacy Assessment**

**12.1.1. Primary Efficacy Endpoint**

■ Percentage Improvement in Dysmenorrhea Relief (%) - 3 months after treatment

**12.1.2. Secondary Efficacy Endpoint**

■ Percentage Improvement in Dysmenorrhea Relief (%) - 1 month after treatment

■ Dysmenorrhea Score

■ Menorrhagia Score

■ Measurement of Quality of Life

- SF36-v2
- UFS-QoL
- SSS
- Uterus size (cm3)
- Satisfaction with the procedure

**12.2. Assessment Criteria and Assessment Method**

<Primary Efficacy Assessment Criteria>

- Percentage Improvement in Dysmenorrhea Relief (%)
  - Definition of dysmenorrhea relief

If the degree of menstrual pain relief corresponds to Minor, Partial, or Complete on the Dysmenorrhea Relief Score

Dysmenorrhea Relief Score

- - Complete relief

② Partial relief

③ Minor relief

④ Ineffective

⑤ Exacerbated pain

- Definition of Percentage Improvement in Dysmenorrhea Relief

Proportion of subjects who met the definition of improvement in dysmenorrhea relief above at 3 months after the procedure

ALPINION Medical Systems Co., Ltd. 28/45

[figure not shown]

[figure not shown]

Protocol No. APM-03 Version 1.10/Date 20180103

[figure not shown]

<Secondary Efficacy Endpoint>

■ Percentage Improvement in Dysmenorrhea Relief (%) - 1 month after treatment

Evaluate the Percentage Improvement in Dysmenorrhea Relief (%) 1 month after the procedure using the same method as that for the primary efficacy endpoint.

■ Dysmenorrhea Score

Subjects directly evaluate dysmenorrhea symptoms on a 5-point scale as shown below before procedure and at 1 and 3 months after the procedure.

Dysmenorrhea Score

1 = Not at all (no symptoms)

2 = A little bit (slight symptoms)

3 = Somewhat (few symptoms)

4 = A great deal (considerable symptoms)

5 = A very great deal (a lot of symptoms)

■ Menorrhagia Score

Subjects directly evaluate menorrhagia symptoms on a 5-point scale as shown below before procedure and at 1 and 3 months after the procedure.

Menorrhagia Score

1 = Not at all (no symptoms)

2 = A little bit (slight symptoms)

3 = Somewhat (few symptoms)

4 = A great deal (considerable symptoms)

5 = A very great deal (a lot of symptoms)

■ Measurement of Quality of Life

Using the questionnaire filled out by the subject, the changes at 1 month and 3 months after the procedure are compared and evaluated before and after the procedure.

- SF36-v2: This is a questionnaire to evaluate the overall quality of life, and consists of 36 questions in 8 domains including physical functioning, role limitation-physical, bodily pain, general health, vitality, social functioning, role limitation-emotional, mental health, and other changes in health condition, etc.
- UFS-QOL: As a questionnaire to evaluate the quality of life related to the symptoms of uterine fibroids, it consists of an 8-item Symptom Severity Score and a 29-item Quality of Life questionnaire.
- SSS (Symptom Severity Score): This is included in the UFS-QOL questionnaire but the severity of symptoms due to uterine fibroids will be evaluated separately.
- Uterus size (cm3)

Compare the overall uterus size immediately after the procedure, at 1 month and 3 months after the procedure.

ALPINION Medical Systems Co., Ltd. 29/45

[figure not shown]

[figure not shown]

Protocol No. APM-03 Version 1.10/Date 20180103

[figure not shown]

- Satisfaction with the procedure

The pain felt by the subject during the procedure and willingness to reuse depending on the satisfaction on the procedure is evaluated through a questionnaire on a 5-point scale.

**12.3. Safety Assessment**

**12.3.1. Safety Endpoints**

All adverse events that occurred to subjects during the clinical trial period

**12.3.2. Assessment Criteria and Assessment Method**

In this clinical trial, adverse events are all undesirable medical findings that cause symptoms not observed before the start of the clinical trial are classified as adverse events. In accordance with the definitions and criteria described in the section ‘15. Assessment Criteria, Assessment Method and Reporting of Safety Including Side Effects’, expected side effects are also classified as adverse events. The severity of adverse events is classified into mild, moderate, and severe, and the use of terms is based on MedDRA’s ‘Preferred term’ and ‘System organ class’.

1. **Data Collection and Statistical Analysis**

**13.1. General Considerations**

All data measured and recorded in this study will be summarized according to the definition of the appropriate analysis sets defined in 14.2. Summary statistics are based on mean ± standard deviation for continuous data and frequency (fraction) for categorical data, and more detailed summary statistics will be presented if necessary.

**13.2. Definition of Analysis Sets**

Efficacy analysis in this clinical trial defines FAS (Full Analysis Set) as the main analysis set, and conducts assessment based on it. As an auxiliary analysis, the same assessment is repeated for the PP analysis set (Per-Protocol Analysis Set). Safety assessment is conducted on all subjects who participated in the study after consent to participate in the study and who received treatment with the investigational medical device.

**13.2.1. Efficacy Analysis Set**

- FAS (Full Analysis Set): As the main analysis set for the assessment of efficacy in this study, it is defined as any subject who participates in the study after consenting to participation, receives the application of investigational medical device, and has at least one valid evaluable data.

ALPINION Medical Systems Co., Ltd. 30/45

[figure not shown]

Protocol No. APM-03 Version 1.10/Date 20180103

- PP analysis set (Per Protocol Analysis Set): It is defined as all subjects who participated in the study after consenting to participate in the study, received the investigational medical device, and completed the clinical study according to the study plan without serious protocol violations until the end of the study. Those who received drugs or alternative treatments that affect efficacy during the clinical trial period are excluded from the PP analysis set.

1. *Major protocol violations to be excluded from the analysis set*
2. Those who received drugs or alternative treatments that affect efficacy during the clinical trial period

**13.2.2. Safety Analysis Set**

■ All subjects who participated in the study after consenting to participate in the study and received treatment with the investigational medical device are included.

**13.2.3. Handling Missing Data (missing values)**

If a missing value occurs in the efficacy endpoints, the variable is excluded from the analysis.

**13.3. Statistical Analysis Method**

**13.3.1. Analysis of General Items**

Data for continuous measurements will be summarized in tables showing mean, standard deviation, median, minimum, maximum and number of subjects. Data for categorical measures will be summarized in tables showing numbers and fractions.

All statistical analyzes will be performed using the SAS statistical program.

**13.3.2. Primary Efficacy Analysis**

■ Percentage Improvement in Dysmenorrhea Relief (%) - 3 months after treatment

The success rate of dysmenorrhea relief will be confirmed based on the following hypothesis.

H0: PA - P0 ≤ - δ vs H1: PA - P0> - δ

- - PA: Expected success rate of the investigational medical device
  - P0: Reference success rate (90%)
  - δ (>0): Non-inferiority threshold (12.3%)

The hypothesis can be expressed as H0: PA ≤ 0.777 vs H1: PA  > 0.777

Therefore, if the lower limit of the 97.5% one-tailed confidence interval of the measured improvement rate (PA) exceeds 0.777, this shows efficacy of the clinical trial.

ALPINION Medical Systems Co., Ltd. 31/45

Protocol No. APM-03 Version 1.10/Date 20180103

**13.3.3. Secondary Efficacy Analysis**

The assessment of the secondary outcome variables considered in this study will be performed at 1 month and 3 months after the procedure, respectively. The ‘satisfaction with the procedure’ is assessed on the day of the procedure.

■ Percentage Improvement in Dysmenorrhea Relief (%) - 1 month after treatment

The same Improvement in Dysmenorrhea Relief as the primary endpoint is obtained at 1 month and a 95% confidence interval is presented.

■ Dysmenorrhea Score - Before procedure, at Months 1 and 3

The change in score at 1 and 3 months after the procedure compared to before the procedure is compared and evaluated using the Wilcoxon signed rank test.

■ Menorrhagia Score - Before procedure, at Months 1 and 3

The change in score at 1 and 3 months after the procedure compared to before the procedure is compared and evaluated using the Wilcoxon signed rank test.

■ Measurement of quality of life (SF36-v2, UFS-QOL, SSS)

Comparison of total and individual item scores for each questionnaire before and after surgery will be analyzed by performing paired t-test or Wilcoxon signed-rank test.

- Uterus size (cm3)

The size of the uterus at 1 month and 3 months after the procedure compared to before the procedure will be compared and evaluated using the paired t-test or Wilcoxon signed rank test.

- Satisfaction with the procedure

The pain and satisfaction scores felt by the subjects during the procedure are summarized as mean and standard deviation.

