**11.1. Study Design**

This clinical trial was designed to evaluate the safety and efficacy of 'ALPIUS 900', a high-intensity focused ultrasound surgical device guided by ultrasound images, for symptomatic patients with adenomyosis. As a prospective, multicenter, single-arm clinical trial, it will be conducted with a total of 80 patients at 2 domestic institutions.

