**11.3. Inclusion and Exclusion Criteria**

**11.3.1. Inclusion Criteria**

Subjects can be enrolled in this clinical trial only if they meet all of the following inclusion criteria.

1. Adult female of at least 20 years of age
2. Pre-menopausal or peri-menopausal (FSH<40mIU/ml)
3. Adenomyosis is clinically diagnosed through MR or US imaging
4. Pain score on the Dysmenorrhea Score is at least 4 points
   - Dysmenorrhea Score

1 = Not at all (no symptoms)

2 = A little bit (slight symptoms)

3 = Somewhat (few symptoms)

4 = A great deal (considerable symptoms)

5 = A very great deal (a lot of symptoms)

1. Have not received any other treatment for adenomyosis within 3 months before HIFU procedure

*☞ In the case of hormone therapy, even within 3 months, subjects can be enrolled if five times the half-life of the drug has elapsed since the last administration.*

ALPINION Medical Systems Co., Ltd. 17/45

[figure not shown]

[figure not shown]

Protocol No. APM-03 Version 1.10/Date 20180103

[figure not shown]

1. Those who voluntarily consent to the clinical trial and are willing to comply with the protocol
2. Those who agree to use a medically accepted method of contraception for the duration of the clinical trial
   - *Medically accepted method of contraception: Physical contraceptive devices other than contraceptives through hormonal control such as condoms or installation of intrauterine contraceptive devices*

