**11.5. Observation Items, Clinical Laboratory Tests and Observation Method**

<Clinical Trial Schedule Table>

[figure not shown]

|  | Screening | Procedure day | Follow-up period | |
| --- | --- | --- | --- | --- |
| Visit day | Visit 1 | Visit 2* | Visit 3 | Visit 4 |
| Days passed | Day -30 to 0 | Day 0 | Month 1 | Month 3 |
| Visit window | - | - | ± 2 weeks | ± 2 weeks |
| Observation type | Clinic visit | Day surgery | Clinic visit | Clinic visit |
| Hospitalization |
|  |  |  |  |
| Obtain consent | √ |  |  |  |
| Inclusion/Exclusion criteria | √ |  |  |  |
| Demographic surveyl | √ |  |  |  |
| Vital signs2 | √ | √ |  |  |
| Physical examination3 | √ |  |  |  |
| Medical history survey4 | √ |  |  |  |
| ECG test5 | √ |  |  |  |
| Laboratory test6 | √ |  | √ |  |
| FSH | √ |  | √ |  |
| Pregnancy test7 | √ |  |  | √ |
| MRI8 | √ | √ | √ | √ |
| U/S9 | √ | √ | √ | √ |
| Dysmenorrhea Relief Score10 |  |  | √ | √ |
| Dysmenorrhea Score 11 | √ |  | √ | √ |
| Menorrhagia Score 12 | √ |  | √ | √ |
| SF36-v213 | √ |  | √ | √ |
| UFS-QoL (including SSS)14 | √ |  | √ | √ |
| US-guided HIFU procedure |  | √ |  |  |
| Subject satisfaction with procedure15 |  | √ |  |  |
| Adverse event/Serious |  | √ | √ | √ |
| adverse event16 |  |
| Concomitant drugs17 | √ | √ | √ | √ |

1. Demographic survey

Basic information of subjects including date of birth, sex, height and body weight

1. Vital signs

Body temperature, blood pressure (systolic/diastolic), pulse, respiration rate

ALPINION Medical Systems Co., Ltd. 20/45

[figure not shown]

[figure not shown]

Protocol No. APM-03 Version 1.10/Date 20180103

[figure not shown]

1. Physical examination

Appearance, skin, head/neck, chest/lung, heart, abdomen, urinary/genital, extremities, musculoskeletal system, nervous system, lymph nodes, other body organs

1. Medical history survey

Survey of medical history during the past 1 year

1. ECG test

Electrocardiography is performed as a screening test for the procedure. If an abnormality is found on the electrocardiogram, the subject cannot be enrolled in this clinical trial.

1. Laboratory test

Laboratory tests are performed on all subjects to evaluate their overall health, and the test items are as follows.

■ Hematology: Hemoglobin, Hematocrit, RBC count, WBC count with differential, platelet

count

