1. U/S

At the screening visit, an ultrasound examination is performed to confirm the size of the uterus and the location of the adenomyoma, and during treatment, the actual treatment is monitored through the image of the ultrasound transducer built into the ALPIUS 900.Immediately after the procedure, the condition of the uterus and adenomyoma after the procedure is checked through ultrasound examination. During the follow-up period, the size of the uterus is checked by ultrasound images at Months 1 and 3. (4 times in total) Contrast agents may be used for ultrasound examination, and detailed examination methods should follow the judgment of the investigator and the standard procedures of the institution.

[figure not shown]

| Product Name | Product Name | Approval No. | Importer |
| --- | --- | --- | --- |
| LOGIQ E9 | Universal ultrasound imaging device | Import Approval No. 09-180 | GE Healthcare Korea Co., Ltd. |

ALPINION Medical Systems Co., Ltd. 21/45

[figure not shown]

[figure not shown]

Protocol No. APM-03 Version 1.10/Date 20180103

[figure not shown]

1. Dysmenorrhea Relief Score

Each subject directly evaluates the degree of dysmenorrhea relief on a 5-point scale using a questionnaire at 1 and 3 months after the procedure.

1. Dysmenorrhea Score

The symptoms of dysmenorrhea are assessed for each subject on a 5-point scale using a questionnaire before the procedure as well as 1 and 3 months after the procedure.

1. Menorrhagia Score

The symptoms of menorrhagia are assessed for each subject on a 5-point scale using a questionnaire before the procedure as well as 1 and 3 months after the procedure.

1. SF36-v2

This is a questionnaire completed directly by the subject to evaluate the overall quality of life, and consists of 36 questions in 8 domains including physical functioning, role limitation-physical, bodily pain, general health, vitality, social functioning, role limitation-emotional, mental health, and other changes in health condition, etc.

1. UFS-QoL (including SSS)

As a questionnaire completed directly by the subject to evaluate the quality of life related to the symptoms of uterine fibroids, it consists of an 8-item Symptom Severity Score and a 29-item Quality of Life questionnaire.

1. Subject satisfaction with procedure

The pain felt by the subject during the procedure and willingness to reuse depending on the satisfaction on the procedure is evaluated through a questionnaire on a 5-point scale.

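### The screening Dysmenorrhea Score that selects women is also the only scheduled baseline for the Month 1 and Month 3 change tests, so the estimated fall is biased towards improvement

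*Protocol*

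**What the plan says.** - **Entry.** Section 11.3.1 requires: "Pain score on the Dysmenorrhea Score is at least 4 points". The scale runs from 1 to 5, so every enrolled woman has a screening score of 4 or 5.
- **Timing.** In the schedule table of section 11.5, the row "Dysmenorrhea Score 11" is ticked at Visit 1 (Day -30 to 0), Month 1 and Month 3. The procedure-day cell is empty, as it is in the synopsis schedule. The note to that row reads: "The symptoms of dysmenorrhea are assessed for each subject on a 5-point scale using a questionnaire before the procedure as well as 1 and 3" (the two closing numbers count months of follow-up).
- **Source of the baseline.** Section 11.6.2 places the symptom ratings at screening, where "questionnaires are used to evaluate the degree of menstrual pain and menorrhagia". On the procedure day, women only "fill out a questionnaire about satisfaction with the procedure before discharge".
- **Analysis.** Section 13.3.3: "The change in score at 1 and 3 months after the procedure compared to before the procedure is compared and evaluated using the Wilcoxon" (that is, by the signed-rank method). It gives no significance level and no success rule for this test.
- **Design.** Section 11.1: "As a prospective, multicenter, single-arm clinical trial, it will be conducted with a total of 80 patients at 2 domestic institutions". The protocol has no run-in and no second baseline.

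**The concern.** A woman's rating of period pain varies from one occasion to the next. Women admitted because one rating was high include some who were caught on a bad occasion, and these tend to rate lower next time without any treatment. Women who would have drifted upward from 1, 2 or 3 are not in the trial. Among those enrolled, a 5 cannot rise and a 4 can rise by only one point.

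The expected change is therefore below zero for an inert device whenever the score is less than perfectly repeatable. The signed rank test takes zero change as its null, so it tests a hypothesis that is already false without a device effect. The estimated fall is also too large.

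This is the only before-and-after measure of the symptom that the primary endpoint addresses, so readers will naturally take it as support for that endpoint. A statistical analysis plan cannot repair it, because a baseline that was never collected cannot be analysed.

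**Working it through.** **1. Sample size used.** The protocol gives no figure for this analysis, so the check uses its evaluable number, 72 (section 11.4). That number reproduces. For a one-sample proportion z-test with the null standard error, null 0.777, true rate 0.90 and one-sided 0.025, the smallest n with exact power of at least 0.80 is 72 (success at 63 or more of 72, power 0.820, actual alpha 0.0262). With 10% dropout, 72 / 0.90 = 80.

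**2. Inputs.** From the protocol: threshold 4 on a 1-5 scale, one pre-treatment score, single arm, signed rank test of the later score against the screening score. Assumed, because the protocol does not state them:
- test-retest correlation r of the underlying symptom: 0.5 to 0.9
- share of candidates scoring at least 4: 30% to 95%
- 40% of those scores being a 5 (varied 20-60%), lower scores split evenly (also varied)
- two-sided 5% level

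**3. Model.** Underlying severity on occasion t is X_t = √r·T + √(1−r)·e_t, with T and e_t independent standard normal. X_t is cut into scores 1 to 5. The first 72 women with a screening score of at least 4 are kept, and the later score minus the screening score is tested. There is no treatment effect and no time trend.

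**4. Bias.** The mean screening score among those enrolled is 0.6 × 4 + 0.4 × 5 = 4.40. If 50% pass and r = 0.7, the mean change is -0.44, so the later mean is 4.40 − 0.44 = 3.96 with no treatment effect. Over 50-70% passing and r = 0.5 to 0.9, the mean change is about -0.12 to -0.68. At 90% passing it is about -0.05 to -0.16.

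**5. Chance of a significant fall at one visit, no treatment effect, n = 72** (nominal 0.025):

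| Share scoring ≥4 | r = 0.5 | r = 0.7 | r = 0.8 | r = 0.9 |
|---|---|---|---|---|
| 30% | 1.00 | 1.00 | 0.99 | 0.87 |
| 50% | 1.00 | 0.97 | 0.87 | 0.67 |
| 70% | 0.93 | 0.79 | 0.62 | 0.40 |
| 80% | 0.69 | 0.53 | 0.43 | 0.26 |
| 90% | 0.32 | 0.22 | 0.20 | 0.10 |
| 95% | 0.13 | 0.09 | 0.10 | 0.06 |

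Small irregularities are simulation error. Using n = 80 or other splits of the scores moves these figures by at most about 0.1 to 0.15. At r = 0.7, the chance that both months are significant is 0.96, 0.64 and 0.07 when 50%, 70% and 90% pass.

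**6. Effect of a separate baseline.** If a second pre-treatment rating with independent occasion noise is the baseline, the mean bias is about 0 and two-sided rejection is 4-6%. That independence needs a new menses between the two ratings. Take 50% passing, r = 0.7 and 25-50% of the noise being rating error (assumed). The chance of a false significant fall is then about 0.11 to 0.23 if half the women have a new menses, and about 0.3 to 0.7 if none do. Under the plan as written it is 0.97.

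**The case against.** **The pass rate may be high.** A reader might infer that the test will usually be significant by selection alone. The documents do not support that. Section 11.2 describes women who need the procedure, section 7.1 calls the symptoms very severe, and section 11.6.2 has women referred after diagnosis. If 90% or more of them already score at least 4, the threshold selects little and the chance falls to about 0.06 to 0.3. This part of the objection stands. What remains is that every scenario examined is above 0.025.

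**It is one secondary analysis.** Section 13.3.2 decides efficacy solely by the lower confidence limit of the relief rate against 0.777. This also stands, and it limits the consequence.

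**The primary endpoint.** A reader might extend the figures to the primary relief rate. They do not carry over. Success there is defined in section 12.2 as: "If the degree of menstrual pain relief corresponds to Minor, Partial, or Complete on the Dysmenorrhea Relief Score". That rating is asked only after the procedure and does not subtract the screening score. Natural fluctuation might colour a woman's answer, but nothing here measures that. Whether minor relief should count, or whether a fall in the Dysmenorrhea Score should also be required, is a separate question about the responder definition.

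**Other uncontrolled influences.** Placebo response and time trend would remain with any baseline. That is correct. A second baseline removes the selection bias, not the lack of a control.

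**Conclusion.** The point holds for the secondary Dysmenorrhea Score analysis. The design facts are in the text: the score is taken once before treatment, that value selects the women, and it is the baseline in a single-arm test. Some bias towards improvement follows as long as the score is not perfectly repeatable.

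Its size depends on two quantities that the protocol does not give. For correlations of 0.6 to 0.9 and an assumed two-sided 5% level, the chance of a false significant fall at one visit is about 0.4 to 1.0 if 30-70% of candidates pass the threshold, and about 0.06 to 0.3 if 90-95% pass. Even the lowest figure, 0.06, is 0.06 / 0.025 = 2.4 times nominal. A significant fall therefore cannot by itself be read as a device effect. Neither the primary analysis nor the sample size is called into question by this calculation.

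**What to change.** - **Schedule (section 11.5, synopsis table, section 11.6.2):** add the one-item Dysmenorrhea Score at Visit 2, answered before sedation and rating the most recent menses.
- **Section 13.3.3:** keep the screening score for eligibility only. Use the Visit 2 score as the baseline for the Month 1 and Month 3 change.
- **New menses:** record whether one occurred between the two ratings, and show the change separately for women who had one. Screening may fall anywhere from Day -30 to Day 0, so some will not.
- **Interpretation:** state that the bias is only partly removed where no new menses occurred, and that the uncontrolled change is not by itself evidence of a device effect.

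The cost is one question at a visit already scheduled, one item on its form and a few lines in section 13.3.3. The reported fall will probably be somewhat smaller. Treatment, sample size and the primary test are unchanged.
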